## Abstract

**Background:**

Chemotherapy-Related Cognitive Impairment (CRCI) significantly impacts the quality of life of breast cancer patients. Triple-negative breast cancer (TNBC) is associated with a higher risk of cognitive decline. The occurrence of CRCI is linked to the expression of inflammatory cytokines. Currently, limited research has examined the efficacy of acupuncture for treating CRCI in TNBC patients. This randomized controlled trial aims to evaluate the effectiveness of acupuncture in managing CRCI among TNBC patients and explore the mechanism by which acupuncture treatment affects CRCI through the inflammatory signaling pathway.

**Methods:**

This study is designed as a prospective, parallel, randomized, sham-controlled, assessor-blinded clinical trial. It will involve 50 patients diagnosed with TNBC who also experience CRCI. Participants will be randomly assigned to two groups, with an equal 1:1 allocation ratio into either the intervention group or the control group. Both groups will receive acupuncture sessions twice weekly for 8 weeks, with each session lasting approximately 20 min. The primary outcome of this study will be the percentage of subjects showing improvement in the Montreal Cognitive Assessment (MoCA) score at the end of treatment. Secondary outcome measures will include the Mini-Mental State Examination (MMSE) score, EORTC QLQ-C30 score, and the expression of inflammatory cytokines.

**Discussion:**

The findings of this study are expected to provide additional evidence supporting the efficacy of acupuncture and contribute clinical data that may elucidate the potential therapeutic mechanisms by which acupuncture ameliorates CRCI.

**Trial registration:**

https://www.chictr.org.cn/showproj.html?proj=218356, identifier: ChiCTR2400080147.

## Introduction

1

Breast cancer remains the primary cause of elevated cancer morbidity and disability among women (1). More than 50% of breast cancer patients undergo chemotherapy treatment (2), with up to 81.4% of patients in China requiring adjuvant chemotherapy (3). Chemotherapy-Related Cognitive Impairment (CRCI) is a common clinical complication in breast cancer survivors. The clinical manifestations encompass a spectrum of neurocognitive symptoms characterized by diminished cognitive function, evidenced by subtle declines in memory, mental clarity, and the capacity to maintain focus or organization during or after chemotherapy (4). Estimates suggest that approximately 75% of patients experience cognitive impairment during chemotherapy, while 35% continue to experience cognitive impairment and a reduced quality of life for several years post-chemotherapy (5). The 5-year relative survival rate for breast cancer patients has improved from 75 to 90% (2). However, CRCI could impede these patients’ reintegration into the workforce. This condition may interfere with adherence to treatment regimens and impact patients’ ability to enjoy an enhanced quality of life and social functioning, potentially leading to further economic consequences (6–8).

Triple-negative breast cancer (TNBC) is a significant risk factor for CRCI. Patients with TNBC exhibit more severe overall cognitive dysfunction and memory impairment compared to non-TNBC patients. Liu Z et al. (9) demonstrated a correlation between hormone receptor and HER2 status and CRCI in breast cancer patients, potentially due to the protective effects of these receptors on cognitive function. Additional research (10) indicates that patients with estrogen receptor (ER) and progesterone receptor (PR) double-negative status are more susceptible to cognitive decline and memory impairment following chemotherapy, compared to those with ER and PR positive status. These observations underscore the strong association between cognitive impairment and hormone receptor status.

Despite substantial evidence indicating the high prevalence of CRCI, there is a notable scarcity of therapies specifically developed to address this condition. Pharmacological interventions have shown no efficacy in preventing or treating CRCI (11). Furthermore, the cognitive benefits of cognitive training and physical activity interventions for individuals experiencing cognitive problems remain ambiguous, and the effectiveness of these interventions requires further demonstration (11, 12).

Acupuncture, a fundamental component of traditional Chinese medicine (TCM), has been utilized for millennia in treating various neurological disorders. Multiple systematic reviews and meta-analyses have demonstrated the efficacy and safety of acupuncture in treating mild cognitive impairment when compared to medication, usual care, and sham acupuncture (13–19). Taishan Tong et al. (19) reported the application of acupuncture therapy for CRCI in breast cancer patients, albeit without follow-up observations. Our previous research (17, 18) also indicated that acupuncture influences overall cognitive function in patients with CRCI, potentially offering complementary therapeutic options. However, current studies lack robust methodological evidence, and the mechanisms underlying acupuncture’s effects remain subject to debate.

Prior research has demonstrated a correlation between the occurrence of CRCI and inflammatory processes, including the activity of cytokines and lymphocytes (20–24). Among the factors contributing to cognitive deficits, oxidative stress and inflammation are considered to be potentially the most significant (25–27). Cytokines are believed to influence cognitive functions through various mechanisms, including the modulation of immune responses, synaptic plasticity, neurotrophic support, neuroinflammatory processes, the maintenance of blood–brain barrier (BBB) integrity, and the regulation of gene expression related to cognition (28).

To the best of our knowledge, cytokines may play a crucial role in the pathogenesis of CRCI. Previous studies have shown that cytokines show different temporal trends during and after chemotherapy, and are associated with specific areas of cognitive impairment (29, 30). IL-6 levels show a biphasic pattern, with consistently increasing concentrations from the start of chemotherapy to 6 months post-chemotherapy, followed by a gradual decline over time after 6 months (29). In contrast, IL-1β and IL-4 levels remain significantly elevated after chemotherapy and are associated with long-term deficits in verbal memory and executive function (30, 31). IL-7 and IL-10 show transient suppression early in the course of chemotherapy, with recovery trajectories associated with improved verbal fluency (30). Several scholars have proposed that a quantitative cytokine level balance or ratio is also associated with the development of CRCI, that cytokines present at different concentration levels in different regions of the brain, and that memory function correlates with optimal concentration levels of specific cytokines (30). TNF-*α* is associated with acute cognitive trajectories (32), and IL-6 and IL-8 are associated with persistent cognitive trajectories (33). Elevated concentrations of IL-6 and IL-1β may result in a decrease in reaction speed and perceptual functioning (33). IL-4 has a protective effect on reaction speed and the higher the concentration, the better the learning ability (32).

However, no study has yet been conducted to elucidate the underlying mechanisms of acupuncture for CRCI based on cytokine activity. Therefore, we will conduct a randomized controlled clinical trial to evaluate the efficacy and safety of acupuncture for the treatment of CRCI in patients with TNBC. This study aims to provide high-level evidence supporting the potential therapeutic mechanisms of acupuncture. Specifically, we seek to elucidate the therapeutic mechanisms of acupuncture for CRCI by examining the expression levels of inflammatory cytokines.

## Methods and analysis

2

### Design and setting

2.1

A parallel, randomized, sham-controlled prospective trial will be conducted in Beijing Hospital of Traditional Chinese Medicine, Capital Medical University. This study is designed as a parallel, single-center, randomized, sham-controlled prospective experiment to evaluate the efficacy of acupuncture treatment for triple-negative breast cancer patients experiencing chemotherapy-induced cognitive impairment. The trial will be conducted from January 22, 2024 to May 1, 2026 at Beijing Hospital of Traditional Chinese Medicine, Capital Medical University. Eligible patients with CRCI will be randomly allocated to either the verum acupuncture group or the sham acupuncture group in a 1:1 ratio. The observation period spans 14 weeks, comprising an 8-week treatment phase followed by a 6-week follow-up phase. Figure 1 illustrates the flowchart of the study procedure, while Table 1 outlines the assessment time points.

**Figure 1 fig1:**
[figure not shown]
Project overview. MOCA, Montreal Cognitive Assessment; MMSE, Mini-Mental State Examination; EORTC QLQ-C30, The European Organization for Research and Treatment of Cancer QLQ-C30; Expression of inflammatory cytokines (TNF-*α*, IL-1β, IL-2, IL-4, IL-5, IL-6, IL-8, IL-10, IL-12p70, IL-17, IFN-*γ*, IFN-α).

**Table 1 tab1:** Schedule of enrollment, interventions, and assessments.

Time point	Baseline	Treatment phase			Follow-up phase
	Week 0	Week 1	→	Week 8	Week 14
Enrollment					
Eligibility screen	×				
Informed consent	×				
Randomization	×				
Interventions					
Verum acupuncture		16 sessions treatment			
Sham acupuncture		16 sessions treatment			
Laboratory test					
Cytokine	×			×	×
Assessments					
MOCA	×			×	×
MMSE	×			×	×
EORTC QLQ-C30	×			×	×
Adverse events		×	→	×	

### Patient

2.2

#### Recruitment strategies

2.2.1

Recruitment of participants will occur through outpatient clinics and wards at Beijing Hospital of Traditional Chinese Medicine, Capital Medical University, utilizing advertisements on posters and via WeChat to ensure an adequate sample size. Research assistants will be deployed to the hospitals to conduct participant screening.

Prior to commencing treatment, participants will undergo a comprehensive baseline assessment, and their cancer history will be meticulously documented. This documentation encompasses details of previous surgeries, pathology reports, and information regarding prior treatments. Additionally, a thorough safety evaluation will be conducted.

#### Inclusion criteria

2.2.2

Patients with histologically, cytologically, or radiographically confirmed triple-negative breast cancer.Age 18–65 years.Patients exhibiting cognitive impairment within 3 years post-chemotherapy and those diagnosed with mild cognitive impairment.The syndrome differentiation according to TCM is of the Qi-Xue-Shi-Tiao type.Patients are expected to have a life expectancy exceeding 1 year.Participants voluntarily enrolled in the study and provided written informed consent.

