### Randomization and blinding

2.3

A computer-generated block randomization with 1:1 allocation will be used to assign 50 eligible participants. An independent statistician at the Beijing Hospital of Traditional Chinese Medicine, Capital Medical University will implement the randomization procedure using SPSS 25.0 statistical software (IBM Corporation, Armonk, NY, United States), employing randomly permuted blocks to ensure allocation concealment. The allocation information will become available only after the randomization procedure. Subsequently, a second individual will employ an opaque envelope containing a randomly sorted distribution card to assign patients to either the verum acupuncture group or the sham acupuncture group, based on their hospital visits. The research assistant responsible for randomization and acupuncturists are not blinded to the participant allocation. The data analysts and outcome assessors will not be aware of the allocated group.

To mitigate potential expectations regarding acupuncture treatment, patients will be informed that they will randomly receive one of two different acupuncture regimens. It is not possible to blind participants, owing to the different acupuncture points of the two groups. To minimize potential communication and interaction among participants, each patient will receive individualized acupuncture treatment and follow-up at separate times in distinct rooms. Due to the inherent nature of acupuncture intervention, blinding the acupuncturist is not feasible. Blinding will be applied to the outcome assessment. Data analysts and outcome evaluators will be blinded to the treatment allocation. Furthermore, to maintain the integrity of the study, communication between acupuncturists, participants, and outcome evaluators will be carefully structured to prevent any exchange of information. The assessor will be arranged to conduct assessment on different days from acupuncture treatment to avoid cross communication among the assessor, acupuncturists, and participants. The assessor will also be instructed not to acquire participants’ treatment information and their needling feelings. Prior to analysis, all data will be anonymized to ensure objectivity.

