## Statistical analysis

4

The statistical analysis will be conducted using Microsoft Excel 2016 and SPSS 25.0 statistical software (IBM Corporation, Armonk, NY, United States). An independent statistician, blinded to group assignment, will perform the statistical analysis. All data will be analyzed according to the intention-to-treat (ITT) protocol, regardless of adherence, provided participants receive at least one acupuncture treatment session and complete a baseline assessment of the primary outcome. Missing values will be imputed using the last observation carried forward method. The per-protocol (PP) population, comprising all randomized patients who completed more than 80% of the treatment procedure, will also be analyzed. All statistical tests will be two-sided, with a *p* value of <0.05 considered statistically significant. Categorical variables will be reported as medians (interquartile ranges), while continuous variables with normal distributions will be presented as means ± standard deviations. The chi-square test or Fisher’s exact test will be employed to compare dichotomous data from baseline demographic and clinical information. Measurement data include various scale scores and indicators of inflammatory cytokine expression levels. For normally distributed variables, an independent samples t-test will be used for between-group comparisons, and a paired samples t-test for within-group comparisons before and after therapy. Comparisons at multiple time points will be made using repeated-measures analysis of variance. The Mann–Whitney U test will be utilized for non-normally distributed variables in intergroup comparisons to analyze changes in efficacy outcomes. The comparison of multiple time points will be based on the generalized estimating equation (GEE). Multiple linear regression analysis will be employed to examine correlations between clinical efficacy and inflammatory cytokines.

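### Paired before-after tests within each arm are planned at p<0.05 with no limit on their use, and arms are compared by unadjusted t-tests, although IL-6 turns inside the entry window

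*Protocol article*

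**What the plan says.** All references are to the protocol article.

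- **Entry window** (Inclusion criteria, 2.2.2): "Patients exhibiting cognitive impairment within 3 years post-chemotherapy and those diagnosed with mild cognitive impairment". No minimum interval since chemotherapy is given.
- **Natural course** (Introduction): IL-6 shows "consistently increasing concentrations from the start of chemotherapy to 6 months post-chemotherapy, followed by a gradual decline over time after 6 months". For cognition, the Introduction reports that "approximately 75% of patients experience cognitive impairment during chemotherapy, while 35% continue to experience cognitive impairment".
- **Allocation** (2.3): "A computer-generated block randomization with 1:1 allocation will be used to assign 50 eligible participants". No stratification factor is named.
- **Analysis** (section 4): "Measurement data include various scale scores and indicators of inflammatory cytokine expression levels". For normally distributed variables among these, the arms are compared by an independent samples t-test. Next to it stands "a paired samples t-test for within-group comparisons before and after therapy". One two-sided threshold of p<0.05 covers all tests. Comparisons over several time points use repeated-measures ANOVA or GEE. No covariate is named.
- **Numbers**: 25 per arm (2.6); cytokines in 15 chosen from each arm (2.7.2.3).
- **Primary outcome** (2.7.1): the week-8 MoCA total effective rate, a responder proportion.

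**The concern.** A sham arm is there so that change under verum can be set against change that would have happened anyway. A paired test within one arm discards that comparison. Natural recovery, regression to the mean in patients enrolled because they are impaired, and practice on a repeated scale all count towards significance.

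The paired tests cover the same scores and cytokines as the between-arm tests, under the same threshold, and nothing marks them as descriptive. The plan therefore leaves room for a significant rise in MoCA or fall in IL-6 within the verum arm to be presented as an effect or a mechanism, even if the sham arm changed as much.

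The mechanism aim is the more exposed of the two. On the protocol's own account, IL-6 is rising in some eligible patients and falling in others, depending on time since chemotherapy. With 15 per arm and an unadjusted comparison, a chance difference between arms in that mix shifts the IL-6 result for a reason unrelated to treatment.

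**Working it through.** **1. The plan's own sample size.** Inputs from 2.6: 13.72% versus 58.33%, two-sided alpha 0.05, power 0.90, 20% attrition. Two-proportion Z formula with unpooled variance:

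n = (1.960 + 1.282)² × [0.1372 × 0.8628 + 0.5833 × 0.4167] / 0.4461² = 10.51 × 0.3614 / 0.1990 = 19.1, so 20 per arm; 20 / 0.80 = 25.

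The stated 25 is reproduced and is not in dispute.

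**2. Within-arm gain that reaches p<0.05 with 25 patients.** Critical mean change = t(0.975; 24) × SD / √25 = 2.064 × SD / 5. The SD of change is not given, so it is assumed:

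| SD of change (assumed) | Critical MoCA gain |
|---|---|
| 2.0 | 0.83 |
| 2.5 | 1.03 |
| 3.0 | 1.24 |

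Section 2.7.1 puts the minimum clinically significant difference at 1.22 points. These are thresholds, not estimates of drift.

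**3. How often drift alone would be significant.** With no treatment effect and a natural drift of d SDs of change, the paired t statistic is noncentral t with n − 1 degrees of freedom and noncentrality d√n. The values of d are assumptions:

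| d | n = 25 | n = 15 |
|---|---|---|
| 0.2 | 16% | 11% |
| 0.3 | 30% | 19% |
| 0.5 | 67% | 44% |

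The nominal rate is 5%. At an SD of 2 to 3, this range of d is a drift of 0.4 (0.2 × 2) to 1.5 (0.5 × 3) MoCA points.

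**4. The randomised comparison under the same conditions.** If both arms truly have the 13.72% effective rate with 25 each, the between-arm test rejects in 5.4% of trials (chi-square) or 1.7% (Fisher). Its level holds.

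**5. Imbalance in the cytokine subset.** Assume that 10 of the 30 patients are within 6 months of chemotherapy and that the subset behaves like a random 15 v 15 split. The number a in one arm is hypergeometric: P(a) = C(10, a) × C(20, 15 − a) / C(30, 15). A gap of 4 or more means a ≤ 3 or a ≥ 7, with total probability 0.245. A gap of 4 is 4/15 = 27 percentage points.

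Such figures depend on whether the early total is odd or even, because the gap has the same parity as the total. With 15 early patients a gap of 3 or more has probability 47%; with 14 or 16 it has 27%, because the smallest qualifying gap is then 4. Without a fixed total (binomial draws, early share 1/6, 1/3 or 1/2), a gap of 20 points or more has probability 22%, 33% or 36% with 15 per arm, and 9%, 18% or 20% with 25 per arm.

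**The case against.** The strongest reply is that the sham arm already deals with natural course. Recovery, regression to the mean and retest gain act in both arms, the primary outcome and the sample size rest on a between-arm comparison, and step 4 shows that its level holds. This stands. A chance imbalance is already allowed for in the error rate of a valid randomised test. It costs precision and is not bias by design. It does not help the paired tests, which use no control.

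Several stronger readings are tempting, and the documents do not support them:

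- *The paired tests count as efficacy evidence.* Section 4 never says so. Its one phrase that ties a test to efficacy outcomes concerns the comparison between groups. What can be said is that the use of the paired tests is not limited.
- *Cognition is shown to recover across the entry window.* The 75% is a prevalence during chemotherapy, before entry opens. Neither it nor the 35% gives a change over 8 or 14 weeks.
- *The cytokines in general change during the window.* The Introduction says "IL-7 and IL-10 show transient suppression early in the course of chemotherapy, with recovery trajectories associated with improved verbal fluency", so the suppression falls in the chemotherapy period and the recovery is not dated. IL-1β and IL-4 are said to stay elevated afterwards. Only IL-6, one of 12 cytokines measured, has a dated turning point inside the window.
- *The 13.72% sham rate measures natural recovery.* The Discussion allows that sham needling may itself act, so the rate cannot isolate natural course.
- *The lack of stratification or of a bar on further chemotherapy is an error.* Unstratified blocks are a legitimate choice in a single-centre trial of 50, and an article may leave rules on other treatment to the full protocol.

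Covariates may also be left to a statistical analysis plan that is not shown. This article, however, itself fixes the unadjusted t-test for the scores and cytokines.

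**Conclusion.** The point holds in a limited form. Section 4 commits to within-arm significance tests that cannot separate treatment from change that would occur anyway, and it sets no limit on how they are used. Under an assumed drift of 0.2 to 0.5 SD they would be significant with no treatment effect in 16% to 67% of trials at n = 25 and 11% to 44% at n = 15. The documents give neither the drift nor the SD of change, so these figures show sensitivity and do not estimate the trial's error rate.

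The unadjusted between-arm comparison is a lesser matter. It leaves the IL-6 result in the 15-per-arm subset open to imbalance across the 6-month turning point: about 25% for a gap of 4 or more, given an assumed 10 of 30 early patients and selection that acts like random allocation. The primary responder comparison is not biased and loses only precision.

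**What to change.** Change the Statistical analysis section in two places:

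1. Report change within each arm descriptively, without p-values or claims of significance. Rest every statement on efficacy or mechanism on the between-arm difference with its 95% CI at weeks 8 and 14.
2. For the continuous MoCA and cytokine comparisons, replace the unadjusted t-test with a model that adjusts for the baseline value and for time since last chemotherapy, prespecified as an indicator of up to 6 months versus more than 6 months. An indicator is preferable to a linear term in months, because one straight line cannot represent a course that rises and then falls.

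The information should be at hand: Recruitment strategies (2.2.1) documents prior treatments at baseline, and the 3-year limit already requires time since chemotherapy to be known. The cost is one or two degrees of freedom, and the indicator will be imprecisely estimated if few patients are early.

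Leave the randomisation scheme and the eligibility criteria as they are. With 20 of 50 patients enrolled (Trial status), changing the scheme for the rest would be a trade-off that the adjustment makes unnecessary. The sample size stays at 50 and the primary responder outcome is untouched.
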